## Discussion

This manuscript describes a protocol for a pilot RCT that will compare the effects of isometric, isotonic concentric and isotonic eccentric rotator cuff contractions when used as part of a semi-standardised exercise-based physiotherapy program in patients diagnosed with SPS. Though research does suggest that exercise is an effective modality in the treatment of this sub-group of patients with shoulder pain [18–22], definitive evidence regarding which specific types of exercise, including intensity, duration and frequency, is lacking [21, 22, 25]. Similarly, though concentric and eccentric loading programs have been widely investigated and compared [22, 62–64], results remain inconclusive. Evidence is emerging on the benefits of isometric exercise in lower limb tendinopathy [30, 35], but there is limited research to date evaluating the effects of this mode of strengthening on rotator cuff tendons [37]. This study seeks to explore whether the isometric exercise group may demonstrate greater immediate improvements in pain and strength compared to either the isotonic concentric or isotonic eccentric groups, and as a result, potentially faster gains in function. Since a full-scale RCT is costly, this pilot study will evaluate whether the study design is feasible, in terms of ease of recruitment, suitability of the assessment algorithm, adherence and compliance to both phases of the treatment intervention, drop out rates and nature and number of adverse events. Increasing evidence suggests that a more individualised approach to therapeutic exercise is warranted in the management of SPS [65]. Since a cohort of patients presenting with SPS is likely to be heterogeneous, at varying stages of the tendinopathy continuum, this study may provide important preliminary information regarding treatment effect sizes of the semi-individualised physiotherapy intervention described, and enable more accurate power calculations for a full-scale RCT.

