The secondary aim is to offer insights into any potential trends in treatment effects observed between the groups, to explore whether faster gains in pain, strength and therefore function are achieved from either of the three exercise interventions. To achieve this aim and facilitate sample size  estimations for a full-scale RCT, data will be collected using the selected clinical outcome measures at specific study time-points, with within-treatment and pre- and post-intervention differences evaluated across the three groups.

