### Participants

Participants will be recruited from a physiotherapy outpatient clinic at a large public hospital and two private physiotherapy clinics, all within metropolitan Melbourne, using internal flyers and social media to promote participation. Since SPS is seen in both general and sporting populations, a combination of public and private sector recruitment sites will ensure a broader pool from which to draw participants. Based on a previous study [15] investigating the use of exercise in SPS with an effect size of 0.66 and maintaining a power of 0.80, calculations indicate a minimum of 30 patients would be required in each group for a full-scale RCT. To determine the feasibility for a full-scale RCT, a sample of 36 across the three groups (12 per group) has been chosen for this pilot study. This is approximately 30% of the calculation for a full-scale RCT [39] with an allowance for drop outs. It is anticipated that this sample size will provide the opportunity to observe recruitment rates using the assessment algorithm, adherence to and compliance with the various components of the intervention, number of participants lost to follow-up and number of adverse events; as well as enable preliminary evaluation of clinical outcome trends while saving the costs associated with a full-scale trial.

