#### Secondary outcomes: shoulder-related symptoms and disability (WORC, SPADI), strength (hand-held dynamometer), pain (NRS/VRS), perceived change (GRCS)

As this is a pilot study, it is not fully powered to determine treatment effects, and any inferential statistics will be used cautiously. Nevertheless, the analysis of between-group changes in secondary outcomes at each of the follow-up time-points may offer insights into possible trends and guide the design of a future full-scale RCT [61]. Similarly, baseline between-group participant characteristics and any associated influence on outcomes may also be observed. All data will be analysed as per-protocol. Analyses of variance (ANOVA) with repeated measures will be undertaken to evaluate trends in between-group changes in secondary outcome scores, with post-hoc analyses using Tukey’s HSD test performed where significant between-group differences are observed. Continuous variables (SPADI, WORC, 11-point NRS, VRS, hand-held dynamometer and GRCS) will be summarised using means and standard deviations, or medians and interquartile range, while categorical variables (gender) will be summarised using frequencies and proportions (and 95% confidence intervals). Analysis will be undertaken using SPSS statistical packages (Version 24, SPSS Inc. Chicago, IL) with estimation of effect sizes and confidence intervals; significance set at *p* < 0.05.

All data will be de-identified with analyses performed by an independent analyst. Groups will be coded and intervention allocation undisclosed so that the analyst is blind to the exercise program being used in any of the groups. Hard data will be stored in a locked cabinet and all soft files held on a password-protected computer accessible only to the research team. The principle investigator will have access to the final datasets. Results will be made available to participants on request and will be published in a peer-reviewed journal.

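### With 12 per arm, the pilot's treatment effect sizes are too imprecise to make the full-scale power calculation more accurate

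*Protocol article*

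**What the plan says.** - **Purpose.** The secondary aim (Background, last paragraph) is to look for trends in treatment effects between the groups. To meet it and to help with sample size "estimations for a full-scale RCT, data will be collected using the selected clinical outcome measures at specific study time-points", differences are to be evaluated across the three groups. The Discussion says the pilot may give preliminary information on treatment effect sizes "and enable more accurate power calculations for a full-scale RCT".
- **Size.** Under Participants, "a sample of 36 across the three groups (12 per group) has been chosen for this pilot study". The planned retention is at least 85% (Outcome measures, Primary outcome), and the analysis is per-protocol.
- **Existing planning value.** Participants already cites an earlier study "with an effect size of 0.66 and maintaining a power of 0.80", from which "calculations indicate a minimum of 30 patients would be required in each group for a full-scale RCT".
- **Analysis.** The secondary-outcomes paragraph of Data management and analysis plans repeated-measures ANOVA, with Tukey's "HSD test performed where significant between-group differences are observed" and "significance set at *p* < 0.05". The same paragraph says the pilot is not fully powered for treatment effects, promises caution with inferential statistics, and plans effect sizes with confidence intervals.

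**The concern.** The full-scale trial already has a planning effect of 0.66. For the pilot to make the power calculation more accurate through its effect sizes, its own estimates would have to be precise enough to confirm or revise that value. Twelve per arm, or about 10 after the planned retention, looks far too few. A team that took the statement at face value could size the next trial on a chance high estimate and run it underpowered. It could equally take a chance low estimate and plan an unaffordable trial, or none.

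The second issue is which estimates a later reader will see. Pairwise tests are run only after a significant overall result, and no candidate primary outcome is named. The plan does not prevent the contrasts that happened to reach significance from becoming the ones used for planning.

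**Working it through.** **Inputs.** Effect 0.66, power 0.80 and 12 per arm (Participants); retention at least 85% (Primary outcome); p < 0.05 (Data management and analysis). Assumed: normal outcomes, equal variances, an unadjusted contrast at one time-point, and 0.66 read as a standardised mean difference d. The article does not state its metric.

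**The plan's own figure.** For two means at 80% power, n per group = 2(z_alpha + z_beta)²/d², corrected for the t distribution. One-sided alpha 0.05 with d = 0.66 gives 30, which reproduces the stated minimum. Two-sided alpha 0.05 gives 38. The article states neither the alpha nor the sidedness of its calculation. Two-sided 0.05 is used below.

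**Precision of a pilot effect.**
- 12 per arm: SE(d) = √(2/12 + 0.66²/48) = √(0.1667 + 0.0091) = 0.42.
- 10 per arm (12 × 0.85 = 10.2): SE(d) = √(2/10 + 0.66²/40) = √(0.2000 + 0.0109) = 0.46.
- An observed d of 0.66 has an exact 95% confidence interval of −0.17 to 1.48 with 12 per arm, and −0.25 to 1.55 with 10. Both lower limits are below zero, so neither gives a finite sample size in the assumed direction.

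**What that does to a sample size.** Three-arm pilots were simulated with true effects (0.66, 0, 0) and 12 per arm. The 10th and 90th percentiles of the estimate are about 0.14 and 1.2.
- d = 0.14: 2(1.960 + 0.842)²/0.14² = 15.70/0.0196 ≈ 801, or 802 with the t correction.
- d = 1.22: 15.70/1.488 ≈ 10.5, or 12 with the t correction.

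So the central 80% of pilots would imply between about 800 and 12 per group. With 10 per arm the range of estimates widens to about 0.08 to 1.28.

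**Bias when every contrast is kept.** The mean estimate is 0.68 and the median 0.67 against a truth of 0.66. The estimate is noisy, but nearly unbiased.

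**Bias if only contrasts after a significant overall test were used.** The overall F test reaches p < 0.05 in 34% of these pilots. In those the estimate averages about 1.06, which implies 15 per group. The true power of 15 per group against 0.66 is 42%, not 80%. Tukey significance needs an observed d of at least 1.00 with 12 per arm. Estimates of the 0.66 contrast that pass both steps average about 1.27.

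**What the pilot can estimate.** With 36 − 3 = 33 residual degrees of freedom, the one-sided upper 80% limit for the pooled SD is √(33/χ²(0.20; 33)) = 1.13 times the estimate. That is tight enough to plan on.

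**The case against.** The strongest case on the other side is that the text is hedged and partly self-protecting. The Discussion says the pilot may provide this information, not that it will. The analysis section admits limited power and promises caution. Data gathered to help sample size estimation include SDs and correlations, which the pilot can supply. A repeated-measures or baseline-adjusted analysis would also be more precise than the unadjusted contrast used here.

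Much of this is fair, but it does not remove the point. The Discussion links effect sizes, not only SDs, to better power calculations. Caution about tests does not make an imprecise estimate usable for planning. On precision, assume a baseline correlation of 0.5 to 0.7. Adjustment then cuts the standard error to about 0.42 × √(1 − 0.5²) = 0.36 or 0.42 × √(1 − 0.7²) = 0.30. Even at 0.30 the middle 80% is 0.66 ± 1.28 × 0.30, or 0.28 to 1.04. Sample size scales as 1/d², so the two ends still differ by (1.04/0.28)² ≈ 14-fold.

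Three stronger readings are tempting and not supported:
- **That the plan sizes the next trial on significant contrasts only.** The significance condition applies to the Tukey tests. Effect sizes and confidence intervals are planned with no such condition, and nowhere does the article say which estimates enter the power calculation.
- **That the next trial would most likely be too small.** This holds only under that selection. With all contrasts kept, about half of pilots overestimate the effect. In the 66% with a non-significant overall test, the estimate averages 0.48, which would make the next trial larger.
- **That 29 separate tests give a 77% chance of a false positive.** This counts every outcome at every time-point. The planned repeated-measures models take an outcome's time-points together, leaving about 17 tests: WORC 1, SPADI 1, pain ratings 3, strength positions 5, GRCS 1, in-session pain 2, in-session strength 4. The chance is then 1 − 0.95^17 = 58% if the tests were independent, and outcomes measured in the same patients are not.

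**Conclusion.** The point holds in a limited form. For treatment effects, the pilot does not have the property the Discussion suggests. If the truth is 0.66, the sample size implied by a pilot estimate ranges from about 800 to 12 per group over the central 80% of outcomes, so the pilot cannot improve on the value already assumed. This needs no selection argument. It rests on the single-time-point assumptions stated above, and baseline adjustment at plausible correlations narrows the range without changing the conclusion.

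Inflation to about 1.06, and with it a trial of 15 per group with 42% power, is a risk that the plan leaves open and not a procedure it states. The primary feasibility aim is unaffected. The matter is worth correcting because it bears on how the next trial is sized and costs almost nothing to fix.

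**What to change.** 1. **Background (secondary aim) and Discussion.** Reword so that, for sample size, the pilot supplies only the pooled SD with an upper confidence limit (1.13 × SD for the one-sided 80% limit at 33 degrees of freedom), the baseline to follow-up correlation, and retention. Remove the suggestion that its effect sizes improve the power calculation.
2. **Target difference.** State that the full-scale trial will be sized on a prespecified important difference for one named candidate primary outcome. WORC at week 6 is one possibility: the article describes WORC as among the most responsive questionnaires and treats week 6 as the primary end-point. The article gives no important difference, so its value and source would have to be added.
3. **Data management and analysis, secondary outcomes.** Report all three pairwise differences with 95% confidence intervals for every outcome, whatever the overall p-value, and label them descriptive.

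The cost is wording and a few more rows in the results tables. No extra participants or measurements are needed. What is given up is the claim that the pilot's effect sizes sharpen the power calculation.

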### Trial status

This trial is due to commence on 19th December 2016.

## Abbreviations

GRCS: Global rating of change scale
NRS: Numerical rating scale
RCT: Randomised controlled trial
SPADI: Shoulder Pain and Disability Index
SPS: Subacromial pain syndrome
VRS: Visual rating scale
WORC: Western Ontario Rotator Cuff Index
